#### Analysis of safety

The incidence of adverse events, both overall and for specific events, will be compared between groups using a χ^2^ or Fisher’s exact test, as appropriate. Any participant attending at least one session of yoga or PT will be included in that group for purpose of analysis.

#### Exploratory analyses

We will also examine an alternative definition of “success” at 12 weeks, defined as ≥30% reduction in pain from baseline and ≥30% improvement in function from baseline [104]. Logistic regression will be used with “success” as the outcome and treatment and potential confounders as covariates. We will also compare the following exploratory outcomes using either linear or logistic regression, as appropriate, with treatment and potential confounders as predictors: fear-avoidance beliefs (FABQ), sleep quality, perceived stress, anxiety, depression, coping skills, self-efficacy, and use of non-study cLBP treatments.

#### Qualitative analyses

Initial transcriptions will be read to draft short interview summaries. To minimize coder drift and assure similar use of codes, an initial coding list will be developed based upon initial interview responses and experiences from our previous studies [26,28]. Two research assistants will draft a summary of predominant themes, and then refine and update the code list. Every third interview will be double coded. As line-by-line coding of transcripts progresses, the research team will meet regularly to update the code list and assure codes are being utilized reliably. Atlas.ti qualitative data analysis software will be used to manage the coding process. Ultimately, line-by-line codes will be grouped into larger categories and themes. Themes will be developed after reviewing code frequencies and merging the highest code yields into distinct thematic categories. Frequency of occurrence will be a means to determine the salience of a code.

#### Sample size considerations

For the co-primary endpoints of change in pain or function from baseline to week 12, we assume a one-sided α error = 0.05. If we assume a minimal clinically significant difference of 2.0 points for the 11-point pain intensity scale, then using a 1.0 point non-inferiority margin for pain is reasonable [103]. If we assume 3.0 points on the 23-point RMDQ scale is a minimal clinical significant difference, then choosing a non-inferiority margin of 1.5 for function is reasonable [105]. A common standard deviation of change in all groups is 2.5 points for the 11-point pain intensity scale and 4.35 points for the 23-point RMDQ function scale [24,26].

Using these assumptions, 108 participants in both the yoga and PT group would provide 90% power to detect whether yoga is truly non-inferior to PT in respect to effect on pain. Similarly, 107 participants in both the yoga and PT group would provide 81% power to detect whether yoga is truly non-inferior to PT in respect to effect on function. Using these sample sizes, we would be able to detect at least a 1.4 unit difference in pain or at least a 2.4 difference in function with 90% power for superiority of yoga or PT compared to education. We inflated these sample sizes in order to protect against an estimated dropout rate of 20%. With this adjustment, the target sample size for the yoga and PT groups is 128 participants each. Using a yoga:PT:education 2:2:1 randomization scheme, we need a total of 320 participants (128 yoga, 128 PT, 64 education). Thus, for the co-primary outcomes of pain and function at 12 weeks, we have adequate power to determine non-inferiority between yoga and PT and superiority of yoga and PT to education*.*

We also anticipate adequate power for the longitudinal analyses of the Maintenance Phase data. Incorporation of repeated measures over time increases power by increasing the “effective sample size,” which is a function of the number of participants and the number of total measurements (0, 6, 12, 26, 40, and 52 weeks). Participants who drop-out or who have missing data can still be included in these analyses.

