### Data analysis

Intention-to-treat (ITT) and per-protocol analyses will be performed for all effectiveness analyses with the ITT analysis considered as the primary method. The ITT analysis will include all patients that participated in the intervention regardless of adherence. Every effort will be made to minimize missing data and participant drop-out or loss to follow-up during the study period. We have accounted for possible drop-out or loss to follow-up by increasing the sample size by 20% in all groups. The “last value carried forward” approach will be used to fill in missing outcome variables; this approach reflects an analysis of the last known value of the outcomes and is thought to be conservative as far as the impact on the treatment effect. If the amount of missing data for outcomes or potential confounders is substantial (i.e., >10%), we will perform an analysis based on multiple imputation for comparison. We will also examine the pattern of missing data in order to discern whether the missing data mechanism could be non-ignorable. A per-protocol analysis will include only those participants who are considered to be adherent to the protocol as defined below.

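### The 20% dropout allowance was multiplied on rather than divided out, so 128 per arm leaves 102 completers (power about 89% for pain, 79% for function); separately, no power is given for meeting both co-primary endpoints.

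*Protocol article*

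**What the plan says.** Under Sample size considerations, the protocol article sets the inputs for yoga versus PT: "we assume a one-sided α error = 0.05"; for the margins, "using a 1.0 point non-inferiority margin for pain is reasonable" and "choosing a non-inferiority margin of 1.5 for function is reasonable"; and for variability, "A common standard deviation of change in all groups is 2.5 points for the 11-point pain intensity scale and 4.35 points" on the RMDQ. From these it derives 108 per arm for 90% power on pain. For function it says that "107 participants in both the yoga and PT group would provide 81% power".

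The dropout step follows: "We inflated these sample sizes in order to protect against an estimated dropout rate of 20" per cent. The result is 128 in each of the yoga and PT arms, 64 in education and 320 in total. The Data analysis section describes the same step as "increasing the sample size by 20% in all groups".

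The sample size section concludes that, for pain and function at 12 weeks, "we have adequate power to determine non-inferiority between yoga and PT". Analyses of Treatment Phase data words the primary hypothesis as non-inferiority of yoga on the co-primary endpoints, reduction in pain and improvement in function.

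**The concern.** A dropout rate of 20% means that 80% of those randomised contribute a 12-week outcome. To finish with N completers, a trial must randomise N/0.8. Adding 20% to N is a different operation and always falls short, because 1.2 × 0.8 = 0.96. The two sections together show that the second operation was used where the first was needed, so the stated power does not match the stated dropout.

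The closing sentence on adequate power raises a second question that does not depend on the first. It covers the co-primary outcomes together, but the figures before it are one per endpoint. If the trial's claim requires both, the relevant probability is lower than either figure. A reader who later sees non-inferiority shown on one endpoint only could weigh that result against power the design did not have.

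**Working it through.** **Inputs** (all from Sample size considerations): one-sided α = 0.05, so z = 1.645; margin 1.0 and SD 2.5 for pain; margin 1.5 and SD 4.35 for function; 20% dropout; 128 per arm. The true yoga–PT difference is not stated. I take it as 0, which reproduces the protocol's figures.

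**Formula.** With n per arm, power = Φ( margin / (SD × √(2/n)) − 1.645 ).

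**Reproducing the stated power**
- Pain, n = 108: SE = 2.5 × √(2/108) = 0.340; 1/0.340 − 1.645 = 1.29; power 90.2% (stated 90%).
- Function, n = 107: SE = 4.35 × √(2/107) = 0.595; 1.5/0.595 − 1.645 = 0.88; power 81.0% (stated 81%).

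Both agree, so the model is the protocol's own.

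**Reproducing 128**
- Multiplying: 107 × 1.2 = 128.4 and 108 × 1.2 = 129.6.
- Dividing: 107/0.8 = 133.75, i.e. 134; 108/0.8 = 135.

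Only 107 × 1.2, rounded down, gives 128. Division would need about 335 to 338 in total at 2:2:1 (134 + 134 + 67, or 135 + 135 + 68).

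**What 128 delivers**
- Completers at 20% dropout: 128 × 0.8 = 102.4, i.e. 102.
- Loss that still leaves the required numbers: 1 − 107/128 = 16.4% (function); 1 − 108/128 = 15.6% (pain).
- Pain, n = 102: SE = 0.350; 1/0.350 − 1.645 = 1.21; power 88.7% (noncentral t: 88.5%).
- Function, n = 102: SE = 0.609; 1.5/0.609 − 1.645 = 0.82; power 79.3% (noncentral t: 79.1%).

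**Superiority over education.** With 102 versus 51 completers, the differences detectable with 90% power are 1.39 (pain) and 2.42 (function), against the stated 1.4 and 2.4. That statement is essentially unaffected.

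**Power for both endpoints.** This is the bivariate normal probability that both tests succeed. The article gives no correlation between the two test statistics, so a range is shown.

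| n per arm | correlation 0 | 0.3 | 0.5 | 0.7 |
|---|---|---|---|---|
| 102 | 70.4% | 72.3% | 73.8% | 75.7% |
| 107 | 72.9% | 74.6% | 76.0% | 77.7% |
| 108 | 73.4% | 75.0% | 76.4% | 78.1% |
| 128 | 81.5% | 82.5% | 83.4% | 84.6% |

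Whatever the correlation, power for both cannot exceed power for function alone (79.3% at 102). Moving from 107–108 to 102 lowers it by 2 to 3 points.

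**If every randomised participant is analysed** (n = 128, same SD, true difference 0): pain, 1/0.3125 − 1.645 = 1.56, power 94.0%; function, 1.5/0.544 − 1.645 = 1.11, power 86.7%.

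**The case against.** Three points on the other side carry weight.

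First, the consequence per endpoint is small. Pain loses about 1 point and function about 2. Function ends just under 80%, but the protocol sets no 80% threshold. This stands.

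Second, 102 may not be the number analysed. The Data analysis section makes intention-to-treat primary and fills missing outcomes by carrying the last value forward. Randomisation follows the baseline survey, so there is normally a value to carry. On that basis up to 128 per arm could enter the test, with about 94% and 87% power. This stands as an upper scenario only. The intention-to-treat set is described as those who took part in the intervention, so some randomised participants may be left out. Carried-forward values may also change the SD and pull the arms together, which is weak reassurance in a non-inferiority test. The sample size section itself treats dropouts as lost, and its figures should be right on that basis.

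Third, the protocol does not misstate power for both endpoints. Its 90% and 81% are correct at 108 and 107 and clearly labelled by endpoint. No both-or-either rule is stated, and an article may leave that rule to the full protocol or SAP. This also stands, so the both-endpoints figure is conditional.

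A reader might infer that the dropout slip pulled power from 81–90% down to 70–76%. The documents do not support that. It compares power for both endpoints with power for each one. Most of the gap comes from requiring both, and 73–78% would remain after the inflation was corrected.

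**Conclusion.** The inflation error holds and is documented by the article's own two descriptions of the step. At the stated 20% dropout, 128 per arm yields 102 completers, not 107–108, and 134–135 would be needed. Power among completers is about 89% (pain) and 79% (function) instead of 90% and 81%. This rests on the protocol's inputs, a true difference of zero, and dropouts contributing nothing. It is a modest numerical error that does not undermine the design.

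Separately, the sentence calling power adequate goes further than the figures before it if the primary hypothesis requires both endpoints. That is the natural reading of the hypothesis as worded, though it is not stated as a rule. On that reading power is about 70–76% at 102 per arm and 73–78% at 107–108, for an assumed correlation of 0 to 0.7.

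**What to change.** Keep 320 and correct the text.

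- In Sample size considerations, state that 20% dropout leaves 102 completers per arm in yoga and PT, with about 89% power for pain and 79% for function. Alternatively, state that the quoted 90% and 81% hold only up to about 16% dropout.
- In Data analysis, change the description of the allowance to match.
- If non-inferiority is to be claimed only when both endpoints meet their margins, say so and qualify the sentence on adequate power with the both-endpoints figure and its correlation assumption.
- If carried-forward values are to be counted, so that all 128 per arm are analysed, give that as a separate scenario (about 94% and 87%) and state that SD and true difference are assumed unchanged.

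Baseline adjustment should not be offered as making up the shortfall. The article gives no baseline-to-follow-up correlation, so the gain cannot be quantified.

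The cost is a few rewritten sentences and slightly less favourable figures, with no added participants and no change of design.

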### Compensation to participants

Participants receive honoraria for participating in the study in the form of store gift cards (e.g., Target, CVS). We give the cards to participants after they complete each survey, according to the following schedule: baseline $50, 6 weeks $50, 12 weeks $100, 26 weeks $50, 40 weeks $50, 52 weeks $100. Each participant interviewed for the qualitative analyses also receives a gift card worth $25. We also encourage participants to update their contact information regularly throughout the study if it changes by giving $5 gift cards for providing verifiable updated contact information (e.g., new cell phone number). Participants receive study interventions (yoga classes, PT sessions, educational materials) and materials (e.g., yoga supplies, PT home practice materials, education book) free of charge.

## Trial status

The study is currently recruiting participants.

## Abbreviations

ANOVA: Analysis of variance; BMC: Boston Medical Center; BUMC: Boston University Medical Campus; cLBP: Chronic low back pain; FABQ: Fear Avoidance Belief Questionnaire; ITT: Intention-to-treat; LBP: Low back pain; MODI: Modified Oswestry Disability Index; NEPT: New England Physical Therapy Plus, Inc.; PI: Principal investigator; PT: Physical therapy; QALY: Quality-adjusted life year; RCT: Randomized controlled trial; RMDQ: Modified Roland-Morris Disability Questionnaire; SF-36: Short Form-36 Questionnaire; TENS: Transcutaneous electrical nerve stimulation.
